## Abstract

**Background:**

Atopic dermatitis (AD) is a chronic and relapsing skin disorder that significantly impairs patients’ quality of life. Long-term biologic therapy provides durable efficacy for AD, but raises concerns related to costs, safety, and withdrawal-associated relapse. Traditional Chinese medicine (TCM) has a long history in AD treatment and is usually integrated with biologic treatment to achieve complementary benefits and provide comprehensive care for patients with AD. However, high-quality evidence supporting its real-world efficacy remains limited.

**Objective:**

This study aims to collect real-world data to evaluate the efficacy and safety of TCM integrated with biologics (TCMIB) in moderate to severe AD, thereby providing methodological insights to obtain high-quality evidence and inform future in-depth research on AD treatment.

**Methods:**

A total of 3500 patients with moderate to severe AD will be classified into 7 groups based on clinical manifestations and receive 16 weeks of treatment followed by 36 weeks of observation. A reduction of 75% or more in eczema area and severity index score from baseline to week 16 is set as the primary outcome. The secondary outcomes include the eczema area and severity index, body surface area, Investigator’s Global Assessment scale, Dermatology Life Quality Index, numerical rating scale for pruritus, Patient-Oriented Eczema Measure, Atopic Dermatitis Control Tool, and TCM syndrome scale. Assessments will be performed at baseline, every 2 weeks until week 16, and then every 4 weeks until week 52. Safety assessments include vital signs, concomitant medications, and adverse events. The SAS software (version 9.4) will be used for data analysis, and a *P* value of less than .05 will be considered statistically significant.

**Results:**

This study has been approved by the institutional review boards of Shanghai Skin Disease Hospital and registered on the International Traditional Medicine Clinical Trial Registry (ITMCTR2025000984). Patient recruitment began in June 2025 and is expected to be completed in January 2028. Data analysis will begin in June 2028. The main results of the study are expected to be submitted for publication in peer-reviewed journals in December 2028.

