## Methods

### Study Design

This is a multicenter, prospective, real-world study that will be conducted at 28 hospitals participating in the National Clinical Research Center for Skin and Immune Diseases Real-World Big Data Collection Platform from October 2024 to September 2028. The hospitals are listed in Table S1 in Multimedia Appendix 1. On the basis of the “disease-syndrome” classification framework, patients will be assigned to 7 groups according to their specific clinical presentations (n=500 per group): heat accumulation in the heart and spleen pattern (group A), heart fire with spleen deficiency pattern (group B), spleen deficiency with dampness pattern (group C), wind heat and dampness pattern (group D), spleen deficiency with blood dryness pattern (group E), spleen and kidney yang deficiency pattern (group F), and other patterns (group G). Patients in all groups will undergo a 16-week treatment phase and then a 36-week follow-up period. Baseline is defined as the time of enrollment (week 0) prior to the initiation of any treatment. Assessments will be conducted at baseline, every 2 weeks until week 16, and then every 4 weeks until week 52. The flowchart of this study is shown in Figure 1.

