## Results

This study was reviewed and received ethics approval in September 2024, was funded in January 2025, and was registered in May 2025. Patient recruitment began in June 2025, with 900 patients recruited as of manuscript submission and is scheduled to conclude in January 2028. Data analysis is planned to commence in June 2028, and the primary results are expected to be submitted to a peer-reviewed journal in December 2028.

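### The stated study period ends in September 2028, but recruitment to January 2028 plus 52 weeks of follow-up runs to about the end of January 2029

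*Protocol article*

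**What the plan says.** Study Design in the protocol article sets the conduct period as "from October 2024 to September 2028". It defines baseline as enrolment (week 0) and adds: "Patients in all groups will undergo a 16-week treatment phase and then a 36-week follow-up period". The limitations paragraph of the Discussion confirms a total of 52 weeks.

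The Abstract (Results) gives the recruitment and analysis dates: "Patient recruitment began in June 2025 and is expected to be completed in January 2028. Data analysis will begin in June 2028". The main Results section repeats them: recruitment "is scheduled to conclude in January 2028. Data analysis is planned to commence in June 2028". Both place submission in December 2028. The Abstract speaks of the main results and the Results section of the primary results.

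The primary outcome is EASI75 at week 16. Secondary outcomes run to week 52. After treatment ends, EASI, BSA, IGA, pruritus NRS and ADCT are assessed every 4 weeks, whereas DLQI, POEM and the TCM scale are assessed only at week 52. Under Safety Assessment, vital signs, concomitant medications and adverse events are likewise scheduled at baseline, during treatment and at week 52.

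**The concern.** The study period, the recruitment end and the follow-up length are all stated, and any two of them determine the third. As written they conflict: patients may enter until January 2028, each is owed 52 weeks, yet conduct closes eight months after the last entry.

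If sites worked to the September 2028 date, late enrolees would lose the end of their follow-up. The loss falls hardest on measures whose only post-treatment assessment is at week 52. For DLQI, POEM and the TCM scale, a patient cut off before week 52 contributes nothing after week 16. The scheduled post-treatment safety review would be lost in the same patients. The secondary objective includes prevention of relapse, so the follow-up period is not incidental to the study's aims. Visits not made before sites close cannot be recovered afterwards.

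**Working it through.** **Inputs, all from the protocol article**

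- Recruitment: June 2025 to January 2028 (Abstract and Results).
- Time zero: enrolment (Study Design).
- Week 16 = 16 × 7 = 112 days; week 52 = 52 × 7 = 364 days.
- Study end: September 2028, taken at its latest as 30 September (Study Design).
- Analysis start June 2028; submission December 2028 (Abstract and Results).
- Planned enrolment: 3500 (Sample Size).

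**Step 1. Visits of the last patients** (date = enrolment + 112 or + 364 days)

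| Enrolled | Week 16 | Week 52 |
|---|---|---|
| 1 January 2028 | 22 April 2028 | 30 December 2028 |
| 31 January 2028 | 22 May 2028 | 29 January 2029 |

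The stated end of September 2028 is therefore not reproduced from the article's own inputs. The last week-52 visit comes 91 to 121 days after 30 September 2028.

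**Step 2. How far the last patients get by the stated end**

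- From 31 January to 30 September 2028: 243 days / 7 = 34.7 weeks.
- From 1 January to 30 September 2028: 273 days / 7 = 39.0 weeks.

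**Step 3. Last enrolment that can complete follow-up**

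30 September 2028 − 364 days = 2 October 2027.

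**Step 4. Share affected at the stated end**

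The article gives no accrual profile, so even accrual is an assumption. Share = (recruitment end − 2 October 2027) / (recruitment end − recruitment start). Only months are stated, so the earliest and latest days are used:

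- Low: 1 June 2025 to 1 January 2028: 91 / 944 = 9.6%; × 3500 ≈ 337.
- High: 30 June 2025 to 31 January 2028: 121 / 945 = 12.8%; × 3500 ≈ 448.

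That is roughly 10 to 13%, or about 340 to 450 patients.

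**Step 5. The other two dates, same method**

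- At 1 June 2028 every patient is past week 16 (last visit 22 May), but those enrolled after 3 June 2027 are short of week 52: 212 / 944 = 22.5% to 242 / 945 = 25.6%, about 790 to 900 patients.
- At 1 December 2028, those enrolled after 3 December 2027 are still short: 29 / 944 = 3.1% to 59 / 945 = 6.2%, about 110 to 220 patients.

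So the June and December 2028 dates allow a complete week-16 analysis but not a complete 52-week analysis.

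**The case against.** The best defence is that the calendar serves the primary objective, which is set at 16 weeks. Analysis in June follows directly on the last week-16 visit in May, and the article promises only main or primary results by December. This stands. A reader might infer that the June start or the December submission is itself an error, but nothing in the article says that either covers the 52-week data.

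A reader might also infer that the 52-week data are lost as a whole, or that unreached visits will be filled by multiple imputation, or that an unplanned second analysis will follow. The documents do not support these readings. Under even accrual, some 87 to 90% of patients still reach week 52 by the stated end. Statistical Analysis says only that reasons for missing data will be examined and multiple imputation used; it does not say that visits not yet due will be imputed. Staging of analyses and data cuts are commonly left to a full protocol or analysis plan, so the article's silence on them is no defect.

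Finally, the September 2028 date may be an administrative window. The period opens in October 2024, before funding (January 2025), registration (May 2025) and recruitment (June 2025), so it does not track patient contact closely. That softens the point without removing it. The plain reading is the period in which the study is conducted, and an administrative window would also need to cover the last visits. Recruitment dates are forecasts, but the stated forecasts should agree with one another.

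**Conclusion.** The point holds as a contradiction between stated dates. A September 2028 end is incompatible with recruitment to January 2028 and 52 weeks of follow-up for every patient, and no other part of the article resolves it. This needs no accrual assumption.

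The size does need one. The figure of about 340 to 450 patients assumes even accrual of 3500 and that conduct really stops on 30 September 2028. Front-loaded accrual would lower it and back-loaded accrual would raise it. The 900 patients reported at manuscript submission do not settle which applies, because the submission date is not given.

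What is at risk is week-52 secondary and safety data in late enrolees. The primary outcome and its timetable are unaffected, so the severity is moderate.

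**What to change.** In Study Design, move the stated study end to after the last week-52 visit, from about February 2029, and schedule the week-52 analysis after that. In the Abstract and Results, label the June 2028 analysis and the December 2028 submission as the week-16 primary analysis.

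The cost is a timeline amendment, a matching registry update and later publication of the 52-week results. The design, sample size and primary analysis do not change.

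Keeping September 2028 instead would mean closing recruitment by about 2 October 2027. That gives up some three to four months of accrual and puts the 3500 target at risk, so extending the study end is the cheaper course. Recruitment is still open, so the change can be made before any visit is lost.

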**Conclusions:**

The anticipated findings of this protocol are projected to furnish strong evidence on the efficacy and safety of TCMIB for moderate to severe AD, potentially contributing to the standardization of TCMIB and optimization of clinical practice.

## Introduction

### Background

Atopic dermatitis (AD) is a chronic and relapsing inflammatory skin disorder that exhibits distinct clinical manifestations across different age groups [1]. Its key features include an eczematous eruption accompanied by intense itch [2]. AD is commonly associated with other atopic conditions, including food allergy, asthma, and allergic rhinitis [3]. Worldwide, AD affects more than 200 million people, with estimated prevalence rates of 15% to 25% in children and 3% to 7% in adults [2]. According to the 2019 Global Burden of Disease study, there were 35.58 million cases of AD and 1.54 million years lived with disability attributable to AD in China [4]. AD imposes a substantial economic burden due to both direct medical costs and decreased productivity [5]. Furthermore, AD significantly impairs the quality of life of patients. Pruritus, depression, sleep disturbance, and anxiety are the most cited impacts of AD causing clinical and humanistic burden [6].

In China, the clinical management of AD adheres to a stepwise treatment based on disease severity [7]. Fundamental therapy includes regular use of moisturizer and emollient, and avoidance of triggering factors. For mild to moderate AD, topical corticosteroids or topical calcineurin inhibitors can be used according to the patient’s age, lesion characteristics, affected areas, and severity of condition. Oral antihistamines may also be prescribed as needed to alleviate pruritus or manage comorbid allergic symptoms. In cases of moderate to severe AD, systemic treatment options are introduced, including immunosuppressants, short-term systemic corticosteroids, phototherapy, Janus kinase inhibitors, and biologic agents [8,9]. Despite the availability of multiple conventional therapies for AD, their efficacy is often limited, or their safety profile is unsatisfactory in some patients with moderate to severe disease, making it difficult to meet the clinical needs [10].

In recent years, the emergence of biologic agents has transformed the AD treatment landscape, enabling patients to achieve a high level of disease control [11]. Expert consensus indicates that biologic agents can be used as first-line systemic therapy for patients with moderate to severe AD with inadequate response to or who are unsuitable for topical therapies [8]. Dupilumab is the first biologic agent approved for AD, which marked the transition from broad-spectrum systemic immunosuppressants to precision-targeted treatment [12]. By targeting interleukin-4 receptor α, dupilumab inhibits the signaling of both interleukin-4 and interleukin-13, thereby reducing inflammatory responses and alleviating pruritus [11]. Stapokibart is the first domestically developed interleukin-4 receptor α antibody drug approved in China, having received regulatory approval in September 2024 for the treatment of moderate to severe AD in adults [13]. Biologics have significantly improved the capacity to achieve treatment goals for AD. However, their risk-benefit profiles still need to be carefully considered due to the high treatment costs, the requirement for biweekly subcutaneous injections, and the potential for disease relapse following discontinuation [14-17]. Consequently, exploring more diverse and sustainable long-term management strategies has become a critical and urgent issue.

Traditional Chinese medicine (TCM) and integrated traditional Chinese and Western medicine (ICWM) offer novel perspectives and directions for the clinical management of AD, especially for patients with moderate to severe AD. TCM has unique clinical advantages in understanding and treating AD. According to TCM theory, the pathogenesis of AD is attributed to internal factors such as heart fire and spleen dampness, as well as external factors such as wind evil [18]. TCM treatment emphasizes syndrome differentiation and holistic regulation, aiming to rebalance the body by addressing immune dysregulation, restoring skin barrier function, and promoting systemic equilibrium. This approach demonstrates considerable advantages in terms of treatment efficacy, reduction in side effects, and prevention of relapse. ICWM represents a treatment model with distinctive Chinese characteristics. For patients with severe AD, TCM integrated with biologics (TCMIB) can facilitate rapid disease control and alleviate clinical symptoms [14]. Previous studies have suggested that combining TCM with dupilumab may offer superior clinical efficacy compared to dupilumab monotherapy in moderate to severe AD, resulting in better lesion clearance, greater itch reduction, and improved quality of life [19,20]. However, due to limited sample sizes and insufficient evidence, definitive conclusions regarding the efficacy and safety of TCMIB for AD cannot be drawn. Therefore, we will conduct a prospective real-world study on patients with AD undergoing TCMIB treatment.

### Objectives

In this study, we plan to collect clinically relevant data from patients in a real-world setting. The primary objective of this study is to evaluate the efficacy and safety of TCMIB treatment at 16 weeks in patients with moderate to severe AD, and the secondary objective is to analyze data on the involvement of TCM in the diagnosis, treatment, constitutional regulation, and prevention of relapse in AD so as to provide methodological insights to obtain high-quality evidence and inform future in-depth research on AD treatment. The findings are expected to provide further evidence for standardizing TCMIB regimens in the treatment of AD.

## Methods

### Study Design

This is a multicenter, prospective, real-world study that will be conducted at 28 hospitals participating in the National Clinical Research Center for Skin and Immune Diseases Real-World Big Data Collection Platform from October 2024 to September 2028. The hospitals are listed in Table S1 in Multimedia Appendix 1. On the basis of the “disease-syndrome” classification framework, patients will be assigned to 7 groups according to their specific clinical presentations (n=500 per group): heat accumulation in the heart and spleen pattern (group A), heart fire with spleen deficiency pattern (group B), spleen deficiency with dampness pattern (group C), wind heat and dampness pattern (group D), spleen deficiency with blood dryness pattern (group E), spleen and kidney yang deficiency pattern (group F), and other patterns (group G). Patients in all groups will undergo a 16-week treatment phase and then a 36-week follow-up period. Baseline is defined as the time of enrollment (week 0) prior to the initiation of any treatment. Assessments will be conducted at baseline, every 2 weeks until week 16, and then every 4 weeks until week 52. The flowchart of this study is shown in Figure 1.

**Figure 1. F1:**
[figure not shown]
Study flowchart. AD: atopic dermatitis; ADCT: Atopic Dermatitis Control Tool; AE: adverse event; BSA: body surface area; DLQI: Dermatology Life Quality Index; EASI: eczema area and severity index; IGA: Investigator’s Global Assessment scale; NRS: numerical rating scale; POEM: Patient-Oriented Eczema Measure; SAE: serious adverse event; SCORAD: Scoring Atopic Dermatitis; TCM: traditional Chinese medicine; WM: Western medicine.

### Diagnostic Criteria, Inclusion Criteria, and Exclusion Criteria

The diagnostic criteria of AD are based on the Chinese Guideline for the Diagnosis and Treatment of Atopic Dermatitis (2020 edition) [9], and the diagnostic criteria of TCM patterns are based on the guidelines for diagnosis and treatment of AD in TCM (DB44/T 2259-2020) [21], a local standard of Guangdong province.

The inclusion criteria for this study are as follows: (1) meeting the diagnostic criteria for AD, (2) a Scoring Atopic Dermatitis score of 25 or higher, (3) a history of Western medicine treatment but without previous TCM treatment, (4) male or female patients over 18 years of age, and (5) signature of the informed consent form.

The exclusion criteria comprise the following: (1) pregnant or lactating women; (2) patients with abnormal hepatic, renal, or hematologic function; (3) patients who previously completed or withdrew from this study; and (4) those currently participating in other clinical trials for AD.

### Treatment Plan

The treatment plans of patients included in the study are formulated in accordance with the expert consensus on TCM diagnosis and treatment of AD [22] and the guidelines for diagnosis and treatment of AD in TCM [21]. Patients in groups A to F will receive both TCM and biologic treatment (TCMIB groups), whereas patients in group G will receive biologic treatment only. TCM prescriptions include Sanxin Daochi decoction, Peitu Qingxin decoction, Xiao’er Huashi decoction, Shenling Baizhu powder, Xiaofeng powder, Jianpi Runfu decoction, Zhenwu decoction, and Wuling powder. All TCM prescriptions are administered as decoctions for oral use. The standard dosage is 1 dose per day, which is decocted in water and divided into 2 warm servings of 200 mL each. Dermatologists are permitted to individualize the base prescriptions according to each patient’s specific pattern differentiation. The biologic agent used in this study is dupilumab. The dosing regimen follows the expert consensus for dupilumab in the treatment of AD [10]: an initial dose of 600 mg (administered as two 300-mg subcutaneous injections) with a maintenance dose of 300 mg subcutaneously every 2 weeks. Patients in all 7 groups will undergo a 16-week treatment phase and then a 36-week follow-up period. Detailed treatment regimens are provided in Table S2 in Multimedia Appendix 1.

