### Sample Size

The improvement of 75% or more in the eczema area and severity index (EASI75) response rate at week 16 will be adopted as the primary efficacy outcome in this study. On the basis of prior data [29], a 57% response rate will be assumed in patients with biologic treatment (group G; *p*_1_= 0.57), and a 70% response rate will be assumed for the TCMIB group (groups A-F; *p*_2_=0.70). A 2-sided significance level (α) of .01 and a statistical power (1 − β) of 0.90 are specified. According to the sample size calculation formula n = (μ_α/2_ + μ_β_)^2^ × [*p*_1_(1 − *p*_1_) + *p*_2_(1 − *p*_2_)]/(*p*_2_ − *p*_1_)^2^, and considering a 15% dropout rate, at least 472 patients should be enrolled in each group. The final sample size is determined to be 500 patients per group. A total of at least 3500 participants are planned to be enrolled. Additionally, each participating hospital is expected to recruit a minimum of 100 patients, with at least 10 patients in each of the 7 treatment groups.

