This protocol outlines the design of a prospective, multicenter, large-scale observational study that provides a real-world setting to explore the role of TCM in the diagnosis and treatment of, constitutional regulation of, and prevention of relapse in AD. To our knowledge, this is the first multicenter observational study in China to enroll at least 3500 patients with moderate to severe AD. The study will analyze the demographic and TCM-specific characteristic profiles of the AD cohort and identify optimal TCMIB therapeutic strategies through long-term observation. Furthermore, it will provide critical data on the effectiveness and safety of a 16-week TCMIB intervention and explore whether this treatment yields additional clinical benefits. Beyond these immediate goals, the creation of a shared clinical database is expected to provide substantial data support for subsequent TCM research, ultimately contributing to the progression of AD clinical research and management.

There are some limitations to this study. First, patient-reported outcomes such as NRS for pruritus and POEM are inherently subjective and may be biased by interindividual differences in symptom perception thresholds. Second, the total period of this study is 52 weeks (including a 16-week treatment period and a 36-week follow-up period). For various reasons, some patients may have difficulty completing the whole study cycle, resulting in loss to follow-up. Third, as this is a real-world study, patients’ treatment regimens are not randomly assigned, making the results susceptible to certain biases. The potential influence of unmeasured confounding factors on the study results cannot be excluded, which poses challenges to causal inference. Fourth, while external TCM treatment methods (eg, topical Chinese medicine and acupuncture) have all shown therapeutic promise in AD [33-35], this study is restricted to oral TCM formulations. This focus limits the comprehensiveness of the assessment regarding the full therapeutic potential of TCM for AD.

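### TCM pattern alone fixes the regimen, so the groups A-F versus group G contrast cannot separate the effect of adding TCM from the effect of pattern without an unstated, untestable assumption

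*Protocol article*

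**What the plan says.** - **How groups are formed (Protocol article, Study Design).** "patients will be assigned to 7 groups according to their specific clinical presentations (n=500 per group". Groups A to F are six named TCM patterns. The last two entries of the list read "spleen and kidney yang deficiency pattern (group F), and other patterns (group G", so G collects everyone who fits none of the six.
- **What each group receives (Treatment Plan).** "Patients in groups A to F will receive both TCM and biologic treatment (TCMIB groups), whereas patients in group G will receive biologic treatment only". The biologic is dupilumab in all groups.
- **The comparison that sets the sample size (Sample Size).** "a 57% response rate will be assumed in patients with biologic treatment (group G" and "a 70% response rate will be assumed for the TCMIB group (groups A-F" for week-16 EASI75. "A 2-sided significance level (α) of .01 and a statistical power (1 − β) of 0.90 are specified". The result is "considering a 15% dropout rate, at least 472 patients should be enrolled in each group", rounded up to 500.
- **The model (Statistical Analysis).** The GEE model for EASI75 has treatment regimen as its independent variable. It adjusts for age, sex, family history, comorbidities, baseline EASI, BSA and IGA, smoking and drinking. TCM pattern is not in the list.
- **The caveat (Discussion, Expected Findings).** "treatment regimens are not randomly assigned, making the results susceptible to certain biases". The same paragraph adds that unmeasured confounding cannot be excluded.

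**The concern.** Study Design and Treatment Plan, read together, make regimen a function of pattern. No patient with a named pattern serves as a dupilumab-only comparator, and no patient in the residual group takes TCM. This differs from ordinary confounding by indication. There, some patients of each kind receive each treatment, and adjustment or weighting can work on that overlap. Here the variable that decides treatment is recorded for everyone but cannot be adjusted for, because there is no overlap on it.

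What is at stake is the meaning of the main comparative result. If the residual-pattern patients respond to dupilumab differently from the six named patterns, that difference enters the estimated TCM effect one for one. A larger sample makes the interval narrower around the biased value.

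**Working it through.** **1. The plan's own figure.** Inputs from Sample Size: p1 = 0.57, p2 = 0.70, two-sided α = .01, power 0.90, dropout 15%.

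n = (2.5758 + 1.2816)² × [0.57 × 0.43 + 0.70 × 0.30] / 0.13² = 14.879 × (0.2451 + 0.2100) / 0.0169 = 400.7, rounded up to 401. Then 401 / 0.85 = 471.8, which rounds up to 472. The stated figure reproduces, so the arithmetic is sound. The point concerns what the contrast estimates.

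**2. Can regimen and pattern both enter a model?** Take seven pattern indicators (A to G) and one regimen indicator (1 for A-F, 0 for G). The regimen indicator is the exact sum of the indicators for A to F. The design matrix has rank 7 with the pattern indicators alone and still rank 7 with regimen added. Once pattern is in the model, a regimen effect is not identified.

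**3. What the contrast contains.** Write Y1 for response on TCM plus dupilumab and Y0 for response on dupilumab alone. Then

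E[Y | A-F] − E[Y | G] = {E[Y1 | A-F] − E[Y0 | A-F]} + {E[Y0 | A-F] − E[Y0 | G]}.

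The first bracket is the add-on effect of TCM. The second is the pattern difference in dupilumab response, and it is the bias. Y0 is never observed in A-F, so the second bracket cannot be estimated from the study. It is zero only by assumption. In the adjusted model the assumption is that it is zero given the listed covariates.

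**4. Illustration of sensitivity.** These inputs are assumptions. The protocol gives no pattern-specific response rates. TCM adds nothing, G responds at 57%, and A-F respond at 57% + d because of pattern. Evaluable patients: 500 × 0.85 = 425 in G and 6 × 425 = 2550 in A-F. No covariate adjustment. With SE = √[0.57 × 0.43 / 425 + p(1 − p) / n₂] and p = 0.57 + d, the chance of a significant apparent benefit is Φ(d / SE − z).

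Worked case, d = 0.05 and n₂ = 2550: SE = √(0.2451 / 425 + 0.62 × 0.38 / 2550) = 0.02587; d / SE = 1.933; Φ(1.933 − 1.960) = 0.489.

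| d (points) | A-F pooled v G, α = .05 | A-F pooled v G, α = .01 | one group of 425 v G, α = .05 |
|---|---|---|---|
| 5 | 49% | 26% | 32% |
| 8 | 87% | 70% | 67% |
| 10 | 97% | 90% | 86% (85% with a pooled SE) |
| 13 | 99.9% | 99% | 98% |

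Both levels are shown because Sample Size uses .01 and Statistical Analysis uses .05. A pattern difference of 13 points would look the same as the whole planned effect.

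**5. The other direction.** Suppose TCM truly adds 13 points and A-F respond 8 points less often than G to dupilumab alone. The visible difference is 13 − 8 = 5 points (62% versus 57%). This is the first row of the table, so a real effect would be detected only about 49% of the time at .05 and 26% at .01 in the pooled comparison.

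**The case against.** The strongest reply has four parts.

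- **The contrast is estimable.** A reader might infer that the TCM effect cannot be estimated at all. The documents do not support that. The A-F versus G difference can be computed, crude or adjusted, and it equals the TCM effect if pattern has no influence on dupilumab response given the covariates. Nothing in the protocol shows that pattern has such an influence, and baseline EASI, BSA and IGA may carry part of any that exists. This stands as a limit on the wording. It does not remove the point, because the protocol never states the assumption and has no data that could test it.
- **It is already disclosed.** Expected Findings admits non-random regimens and, separately, unmeasured confounding as a difficulty for causal inference. That is partial disclosure. It does not say that a measured variable fully determines treatment, so a reader would expect adjustment to help where it cannot.
- **The study is modest in aim.** The primary objective names no comparator, the Discussion speaks of exploring additional benefit, and the article's closing Conclusions promise only further evidence. A reader might infer that the whole article claims strong evidence, but only the abstract's Conclusions do. Even so, the sample size rests on A-F versus G and regimen is the exposure in the model, so the comparative reading is the study's own.
- **The size is hypothetical.** Correct. The differences of 5 to 13 points have no anchor in the protocol, and the pooled comparison at .05 gives the largest percentages. They show sensitivity and predict nothing.

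Figure 1 and Table S2 were not available. The visible text states the allocation without exception. A separate analysis plan could not supply the missing overlap.

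**Conclusion.** The point holds in this form: as designed, the planned contrast and the GEE regimen effect cannot separate adding TCM from TCM pattern, unless pattern is assumed irrelevant to EASI75 response on dupilumab given the listed covariates. The bias equals the pattern difference in dupilumab response, may have either sign, and does not shrink with sample size. Its actual value is unknown. The step from the documents to this conclusion needs only Study Design and Treatment Plan to be taken as written; the percentages rest on the assumed differences, no TCM effect, 15% dropout and no adjustment. The documents do not support saying that the groups cannot be compared, that pattern is known to change dupilumab response, or that a false positive is likely.

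**What to change.** **Change the claim.** In Sample Size, Statistical Analysis, the limitations paragraph of Expected Findings and the abstract's Conclusions:

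- state that A-F versus G is descriptive and will not be read as the effect of adding TCM;
- name the fact that pattern determines regimen, and the assumption that a causal reading would need;
- report EASI75 for each of the seven groups with confidence intervals.

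This needs no new patients or procedures. The cost is a weaker claim. With 900 of 3500 patients recruited at submission, the wording can be settled well before the planned analysis.

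**Optional, for the sponsor to decide.** If patients with patterns A-F who take dupilumab without TCM already occur in routine care at the sites, they could be recorded with their pattern and the primary contrast made within pattern. This is not free. Patients already in G, and any with other patterns, cannot serve as within-pattern comparators, so comparator size and precision would have to be restated. For scale, if 500 such patients were spread evenly over six patterns (an assumption), that is 500 / 6 ≈ 83 per pattern, or about 71 after 15% dropout. Whether such patients exist at the sites cannot be judged from the protocol.
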